## Abstract

**Electronic supplementary material:**

The online version of this article (doi:10.1007/s12265-016-9685-1) contains supplementary material, which is available to authorized users.

## Introduction

Atrial fibrillation (AF) is characterized by beat-to-beat changes in the pattern of activation within the atria, unlike organized arrhythmias such as atrial flutter and atrial tachycardia. This chaotic nature poses a challenge with regard to understanding the pathophysiology and effective treatment of AF as shown by the frequent recurrences after AF therapy [1–4]. Due to the limited knowledge about the mechanisms involved, each AF patient is currently approached in the same manner. Based on the symptomatology and a clinical assessment the arrhythmia is either accepted or attempts are made to retain sinus rhythm with non-selective treatment modalities. However, this approach does not take account of the diversity among AF patients. AF occurs, for example, in association with mitral valve disease, hypertension, congenital heart disease, or cardiac surgery, or in young or older patients without any comorbidity (“lone AF”) [5, 6]. Furthermore, AF can have different clinical manifestations including paroxysmal, persistent, or longstanding persistent. On the structural level, the degree of fibrotic tissue in AF patients demonstrated heterogeneity as well and does not always predict the severity of the AF burden [7]. Therefore, it is likely that the pathophysiological mechanisms may differ between patients with AF. If these can be unraveled the possibility for targeted treatments may arise.

So far, several ablation procedures have been developed aiming to ablate a trigger site for initiation of AF or an arrhythmogenic substrate perpetuating AF. The isolation of triggers residing in the pulmonary veins demonstrated to be most successful in patients with paroxysmal AF. Nonetheless, recurrences occur frequently especially in patients with persistent AF, suggesting an incomplete eradication, reformation, or progression of the arrhythmogenic substrate. Other strategies include the ablation of rotors, ganglionated plexi, and complex fractionated electrograms [8–10]. However, these therapies have similar, limited success rates and there are no guidelines as to which strategy to choose for an individual patient.

The present study has been designed to identify the arrhythmogenic substrate in individual AF patients with the use of a high-resolution epicardial mapping approach. In previous studies, high-resolution epicardial mapping of patients with Wolf-Parkinson-White syndrome or longstanding persistent AF demonstrated to be a valuable tool in discriminating between patients [11, 12]. However, mapping was performed at only three locations and in a limited number of patients with a variety of heart disorders. In this study, subjects are categorized according to the underlying heart disorder(s) and predisposition for developing spontaneous episodes of AF before or after cardiac surgery and epicardial mapping will be performed of the entire epicardial surface [13, 14]. The electrophysiological properties of the atria will be analyzed aiming to find the arrhythmogenic substrate and to contribute to the current knowledge of the pathophysiology of AF.

## Methods

### Study Population

All patients 18 years and older, with structural or coronary heart disease scheduled for elective cardiac surgery will be asked to participate. Patients who have a high-risk of complications during surgery or hemodynamic instability by inducing AF such as Wolff-Parkinson-White syndrome, poor left ventricular function (<40 %), presence of assist devices, hemodynamic instability, usage of inotropic agents, and kidney or liver failure are excluded from this study. Furthermore, patients with medical histories predisposing them for adhesions making epicardial mapping unfeasible or presence of an iatrogenically altered atrial electrophysiology such as prior radiation of the chest for malignancies, redo-cardiac surgery, paced atrial rhythms, and prior ablative therapy in the atria are excluded as well. Each patient, prior to enrolling in the study, will be provided with a written explanation of the study procedure together with an assessment of risks in participating in the study. Patients will be enrolled after the written informed consent form is signed. After enrollment patients are assigned to a group according to the underlying heart disease and whether their medical history includes AF. These groups consist of the following surgical procedures: coronary artery bypass grafting (CABG), mitral valve surgery, aortic valve surgery, mitral valve surgery with CABG, aortic valve surgery with CABG, and congenital heart surgery. Each of these groups are divided into separate groups for patients with and without prior AF episodes. Figure 1 demonstrates the inclusion and following procedures for patients participating in the study.

**Fig. 1 Fig1:**
[figure not shown]
Flow-chart of patient inclusion and following study procedures. After enrollment, patients are assigned to 1 of 12 groups for data analysis according to the presence of previous atrial fibrillation (*AF*) occurrence and the type of surgery that will be performed (i.e., underlying heart disease). Subsequently, all patients are mapped during surgery and continuously monitored after surgery to detect postoperative AF. During the 5-year follow-up (*FU*), the additional tests consist of an electrocardiogram (*ECG*) and Holter monitoring when patients indicate symptoms suspected of AF. *ICF* informed consent form, *CABG* coronary artery bypass grafting, *MV* mitral valve surgery, *AV* aortic valve surgery, *CHD* congenital heart disease

### Study Procedure

Epicardial mapping is performed during open heart surgery [13]. Patients will be under general anesthesia and vital signs will be monitored continuously throughout the procedure. Mapping will be performed before going on extracorporeal circulation, during sinus rhythm, and (induced) AF. AF is induced by fixed rate pacing at the right atrial appendage with a pulse width of 2 ms delivered by temporary pacemaker wires. Pacing bursts will start at a rate of 250 bpm and will be increased with steps of 50 bpm each time AF is not induced after 3 attempts. If AF is not induced at a pacing rate of 400 bpm or loss of capture occurs, attempts will be terminated. As AF is induced it may terminate spontaneously, otherwise, if an induced arrhythmia sustains after the mapping procedure, electrical cardioversion will be performed immediately afterwards. If a patient is in AF at the onset of the mapping procedure, mapping will be performed during AF and during sinus rhythm after electrical cardioversion if there is no atrial thrombus present on transesophageal echocardiogram.

Epicardial mapping of the right and left atria will be performed using a custom-made electrode array (192 electrodes, diameter 0.45 mm, 2-mm inter-electrode distance; GS Swiss, Küssnacht, Swiss). All electrograms recorded by the electrode are stored on hard disk after amplification (gain 1000), filtering (bandwidth 0.5–400 Hz), sampling (1 KHz) and analogue to digital conversion (16 bits). An indifferent electrode is attached to a steal wire fixed in subcutaneous tissue and a reference signal is attached to the right atrium. In addition, a ventricular surface electrocardiogram (ECG) is recorded simultaneously. Signals will be recorded at 9 right and left atrial sites during sinus rhythm for 5 s per site and during (induced) AF for 10 s per site. Mapping is initiated at the lower right atrium and is proceeded upwards over the right atrial appendage. Thereafter, the left atrium will be mapped starting between the pulmonary veins and will continue along the atrioventricular groove from the lower pulmonary veins to the left atrial appendage and finally at the roof of the left atrium for Bachmann’s bundle. The mapping positions are demonstrated on a 3D model in the online Supplementary Video (1). The entire mapping procedure will not prolong the surgical procedure by more than 10–15 min [13].

### Follow-up and Study Endpoint

The postoperative heart rhythm is continuously monitored until hospital discharge and rhythm registrations will be stored in order to determine the incidence of early postoperative AF. After discharge, all patients will be scheduled to visit an out-patient clinic, two times during the first year and thereafter once a year during the following 4 years. Clinical history focused on tachyarrhythmias will be taken and a surface ECG will be made. If indicated, a 24-h Holter recording will be performed. If patients, for any reason, are unable to visit the out-patient clinic, follow-up is done by telephone. In the event that documented rhythm disorders have occurred, records will be requested from the visited hospital. The main endpoint of the study is reached when persistent AF develops.

### Data and Statistical Analysis

Local activation times of the recorded atrial signals will be marked, from which color-coded activation and wave maps will be reconstructed by custom-made software which has previously been described in more detail [11]. Data exclusion criteria include progressive in- or decrease in AF cycle length (AFCL) between sequential recordings (recorded via the reference signal) indicated by an approximately two times in- or decrease in AFCL, recordings of other rhythms than sinus rhythm or AF, or ≥50 % of missing recording data. Data analysis and the criteria for data inclusion are demonstrated in Fig. 2. Electrophysiological parameters that will be derived include conduction velocity, incidence of conduction block, number of fibrillation waves, incidence of epicardial breakthroughs, AFCL, dominant frequency, electrogram voltage (the amplitude of the highest deflection in case of fractionation) and fractionation [11, 12]. For analysis, the electrodes of the mapping array are assigned to quadrants of 1 cm^2^. The variables will consist of averaged values or the percentage of occurrence/incidence for each quadrant. Figure 3 illustrates the construction of an activation map during sinus rhythm, quadrant partition, and its conversion into various parameters of all atrial sites. Figure 4 shows a wave map during AF and the variables that will be analyzed. Furthermore, rotor occurrence and the relation between patterns of activation, fractionation, fibrillation intervals, conduction abnormalities, and voltage will be studied and compared between the different atrial sites, atrial rhythms, and patient groups. Rotors will be defined as a wave of excitation rotating around a phase singularity for one or more cycles [15] and analyzed by determining the dominant frequencies at each recording site in order to identify high-to-low frequency gradients and determination of the degree of linking of fibrillation waves, indicative of repetitive patterns of activation. Linear regression analysis and paired Student’s *t* test will be used to compare various electrophysiological parameters between different sites and different atrial rhythms. Unpaired Student’s *t* test will be used to compare various electrophysiological parameters between patient groups.

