### Study Limitations

Currently, epicardial mapping can only be performed during open-chest cardiac surgery. Therefore, it is not possible to perform epicardial mapping in patients with nondiseased hearts. However, with constantly advancing techniques it may become possible in the future to perform epicardial mappings during video-assisted thoracoscopic surgery in patients without any heart disease. Secondly, although epicardial mapping can reach sites endocardial mapping cannot, some sites are not accessible, for example, the atrial septum. Therefore, epicardial mapping is not able to analyze conduction in the entire area of the atria. In addition, recordings are performed sequentially, as simultaneous high-resolution mapping of the entire surface is not possible yet with currently available technical equipment. As time during surgery is limited, mapping is performed immediately after AF induction or electrical conversion. Consequently, if a progressive increase, or decrease in AFCL occurs during the recordings, this data will have to be excluded [26–28]. General anesthesia may also increase AFCL [29]. However, the same anesthetic protocol is applied in all patients and previous studies have shown that there remain differences in AF between patients despite anesthesia [11, 12]. Furthermore, recent studies have shown that endo-epicardial dissociation can occur during AF and might be associated with persistent AF [30]. This suggests that it is important to investigate endocardial and epicardial conduction simultaneously as conduction can be disturbed in all three dimensions. Finally, there is a small chance asymptomatic persistent AF episodes may be undetected during follow-up. The measured incidence of persistent late postoperative AF may therefore underestimate the true incidence of persistent late postoperative AF.

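### Atrial sites are mapped in one fixed order and AFCL drift is screened only at about two-fold, so the planned between-site AFCL and frequency comparisons are confounded with recording order; site values should be set against the concurrent reference signal

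*Protocol article*

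**What the plan says.** All places are in the protocol article.

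- **Order (Study Procedure).** "Mapping is initiated at the lower right atrium and is proceeded upwards over the right atrial appendage". Left atrial sites follow, and Bachmann's bundle, at the left atrial roof, comes last. No reversed or varied order is described.
- **Sequential recording (Study Limitations).** The authors state that "recordings are performed sequentially, as simultaneous high-resolution mapping of the entire surface is not possible yet". They add that mapping begins directly after AF is induced. No settling period is mentioned.
- **Duration (Study Procedure).** Nine sites are recorded, for 10 s each in AF. The whole procedure has an upper bound: "The entire mapping procedure will not prolong the surgical procedure by more than 10–15 min".
- **Use (Data and Statistical Analysis).** AFCL and dominant frequency are among the derived parameters. Sites are compared by linear regression and paired t test. Rotors are analysed partly by "determining the dominant frequencies at each recording site in order to identify high-to-low frequency gradients".
- **Protection (Data and Statistical Analysis).** Data are excluded for a progressive AFCL change between successive recordings, judged on the reference signal and "indicated by an approximately two times in- or decrease in AFCL". No adjustment of site values for order, time or reference AFCL is named.
- **Restatement (Study Limitations).** "if a progressive increase, or decrease in AFCL occurs during the recordings, this data will have to be excluded", without a figure.
- **Reference (Study Procedure).** A reference signal is attached to the right atrium.

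**The concern.** A frequency gradient between two sites means something spatial only if the AF was in the same state when both were recorded. Here a later site is always a different site. If AFCL lengthens or shortens as mapping proceeds, sites late in the sequence differ from early ones even when the atria are uniform. The authors accept this mechanism, because they exclude data for it. The open question is whether a limit of about two-fold is enough.

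Two results are at stake. One is the within-patient frequency gradient used in the rotor analysis. The other is the group-level comparison of right atrium, left atrium and Bachmann's bundle on AFCL and dominant frequency.

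**Working it through.** **The plan's own figures.** The only figure that bears on drift is the two-fold limit. The sample-size figures concern proportions and play no part here. They do reproduce: 1.96 × √(0.25/50) = 13.9% and 1.96 × √(0.25/300) = 5.7%, stated as 14% and 6%.

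**Step 1: what passes the limit within one patient.** Assume no true gradient, drift shared by all sites, and dominant frequency DF = 1000/AFCL (ms to Hz). The drift sizes are illustrations inside the plan's limit, not observed values.

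- AFCL 200 → 150 ms (1.33-fold): 5.0 → 6.7 Hz, +33%.
- AFCL 200 → 110 ms (1.82-fold): 5.0 → 9.1 Hz, +82%.
- The limit itself, 200 → 100 ms: 5.0 → 10 Hz.

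For AFCL that lengthens by a total factor f, steadily on the log scale over nine ordered sites, the value at site i (i = 0 to 8) is f^(i/8). The apparent first-to-last DF change is 1/f − 1. For shortening by the same factor it is f − 1.

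| Total drift f | DF change, AFCL lengthens | DF change, AFCL shortens | Mean AFCL, last 5 vs first 4 sites (lengthening) |
|---|---|---|---|
| 1.10 | −9% | +10% | +6% |
| 1.25 | −20% | +25% | +13% |
| 1.50 | −33% | +50% | +26% |
| 1.75 | −43% | +75% | +37% |
| 1.99 | −50% | +99% | +48% |

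The 4/5 split is by recording order. How the nine sites divide between the atria is not given in the text.

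**Step 2: the interval is unclear.** If the two-fold check applies to adjacent recordings, a 10% rise at each step passes every check, yet over eight steps it totals 1.10^8 = 2.14-fold.

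**Step 3: effect on a group paired t test.** A simulation of 4,000 runs with 50 patients compared the last five with the first four sites on log AFCL. It had no true site effect and excluded patients at or beyond two-fold drift. Assumptions not in the documents: SD of log drift between patients 0.20, site noise SD 0.08, reference noise SD 0.05, drift shared by all sites.

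| Median total drift | Spurious AFCL difference, raw | False positives, raw | False positives, site relative to reference |
|---|---|---|---|
| 0% | 0% | 4.9% | 5.2% |
| 5% | 2.7% | 31% | 5.1% |
| 10% | 5.4% | 84% | 5.6% |
| 20% | 10.6% | >99.9% | 4.7% |

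Hand check of the 10% row: mean recording position is 0.75 of the series for the last five sites and 0.1875 for the first four, a gap of 0.5625. Expected bias is 0.5625 × ln 1.10 = 0.054 on the log scale, or 5.5%, against 5.4% simulated.

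**Step 4: what the zero row shows.** When drift varies in sign around zero, the raw group test keeps its nominal error rate. Drift then adds noise to the group comparison but still distorts each patient's own gradient.

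**The case against.** **Disclosure and aim.** Study Limitations discloses sequential mapping, immediate recording and AFCL drift, and the study is described as exploratory. That excuses imprecision. It does not excuse a bias that data already collected could reduce. It is also fair that a condensed article may leave an adjustment to a fuller document. The point therefore rests on what the article does state: the fixed order, the loose limit and the between-site comparisons.

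**Stronger readings that a reader might infer, and that the documents do not support:**

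- *Spatial gradients and drift cannot be separated.* The confounding is in the analysis as written, not in the data. The right atrial reference is the article's own source for judging AFCL between recordings, so drift shared by both atria is measurable and removable.
- *Every patient shows a false right-to-left gradient.* No size or direction of drift is given. The article also allows some patients to be in AF at onset and others to be induced, but says nothing on whether drift differs between them.
- *Anything below two-fold is certain to be retained.* The limit is approximate and the Fig. 2 legend has all data checked by hand, so a 1.82-fold change might be removed. No criterion for that is stated.
- *Methods and Limitations set conflicting rules.* Both speak of a progressive change. Limitations more plausibly shortens the Methods rule than replaces it.
- *The rotor analysis as a whole is compromised.* Rotors are defined by rotation around a phase singularity and are also studied through linking of waves. Within one array position the electrodes record together, so that evidence is not confounded with order.
- *The reference signal serves only the exclusion.* The Fig. 2 legend gives it a second use, in checking position in sinus rhythm.

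**Conclusion.** The concern holds in a limited form. Site is confounded with recording order in the planned AF comparisons, and the stated safeguard lets sizeable shared drift through: 1.25-fold drift alone gives a 20% to 25% apparent first-to-last frequency change with no true gradient. Within a patient this follows whenever drift occurs. At group level it becomes bias only if drift tends in one direction.

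The arithmetic assumes drift common to all sites and frequency inverse to AFCL. The false-positive rates also depend on assumed variances. They show that modest one-directional drift would matter; they do not estimate what happens in this study. The actual bias is unknown. This is a cheap improvement to the analysis, not a flaw that invalidates the study.

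**What to change.** 1. For between-site comparisons and frequency gradients in AF, express each site's AFCL and dominant frequency as a ratio to, or difference from, the same quantity in the right atrial reference over the same recording. Report this beside the raw values.
2. State the AFCL drift limit as one number, judged on the reference signal over the whole recording series. Use the same wording in Data and Statistical Analysis and in Study Limitations.
3. Repeat the between-site analyses at a tighter limit as a sensitivity analysis.
4. Do not rely on recording order as a covariate. With a fixed order it is collinear with site, so a model with site as a factor cannot estimate it. Time since induction is no general substitute, because patients already in AF at onset have no induction time.

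**Cost.** No new recordings appear to be needed, since the reference is already used to judge AFCL. The work is one derived variable and one extra set of tables. The reference adds some noise: under the assumed SDs, per-site noise rises from 0.08 to √(0.08² + 0.05²) = 0.094. Drift that the right atrial reference does not follow stays uncorrected and should be named as a remaining limitation.

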**Fig. 3 Fig3:**
[figure not shown]
*Left*: activation map constructed during sinus rhythm. The atrial complexes (*A*) of all 192 recordings are automatically detected and marked at the steepest deflection. The electrode with the earliest atrial marking is set at time (*T*) 0. Activation times of the other electrodes are in reference to T_0_. Isochrones are set at 5 ms intervals after T_0_. The *black/white arrow* illustrates the direction of conduction. Conduction block (<18 cm/s) is represented by *thick black lines. V* ventricular complex. *Right*: The mapping surface is divided into quadrants and parameters such as block %, and mean voltage are determined for each quadrant of each mapping location (total: 36 quadrants). *LA* left atrium, *PV* pulmonary veins, *BB* Bachmann’s bundle, *RA* right atrium

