### The Arrhythmogenic Substrate in AF

The heterogeneous nature in which AF presents and the frequently failing AF treatments so far, demonstrate the importance for an individualized strategy in the treatment of AF. The first step is a better understanding of the pathophysiology underlying initiation and perpetuation of AF. The focus for initiation of AF often originates in the pulmonary veins and Moe et al. described the concept of self-sustaining fibrillatory waves responsible for perpetuation of AF [21, 22]. However, recurrences of persistent AF after successful isolation of the pulmonary veins cannot be explained by these concepts alone. The occurrence of longitudinal dissociation during AF was demonstrated later on and showed to be most prominent in persistent AF [11]. Furthermore, focal fibrillation waves emerging within the recording area, referred to as epicardial breakthroughs, occur much more frequently during persistent AF than during acute AF [12], as well as drivers such as rotors and focal sources [23]. These findings suggest that progressive electro-pathological changes within the atria are associated with persistent AF. Nonetheless, the exact pathophysiological changes and locations at which they occur are not yet known. The underlying diseases most likely initiate different pathophysiological mechanisms that lead to AF. For example, valvular disorders give rise to atrial pressure or volume overload, coronary artery disease can cause atrial ischemia and infarction, and congenital heart diseases may also include congenital atrial abnormalities. For this reason, the patients in this study are divided in separate groups according to the underlying heart disorders and AF occurrence prior to surgery.

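### Two-group t tests between patient groups cannot use the six-disease by AF-history design or adjust for age, so a parameter that only tracks age could be reported as discriminating between diseases

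*Protocol article*

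**What the plan says.** In Study Population, patients are classified by type of surgery (CABG, mitral valve, aortic valve, each valve operation combined with CABG, and congenital), and "Each of these groups are divided into separate groups for patients with and without prior AF episodes". The Fig. 1 legend confirms that "patients are assigned to 1 of 12 groups for data analysis according to the presence of previous atrial fibrillation" and type of surgery. Membership follows from the patient's disease and history, not from randomisation. All adults from 18 years are eligible, with no upper age limit.

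Data and Statistical Analysis assigns methods by type of comparison. For linear regression and the paired t test, the article says the "test will be used to compare various electrophysiological parameters between different sites and different atrial rhythms". For patient groups it names only the unpaired Student's t test, which "test will be used to compare various electrophysiological parameters between patient groups". No covariate or factorial model is attached to the group comparison.

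The Discussion gives the reason for the grouping: "The underlying diseases most likely initiate different pathophysiological mechanisms that lead to AF".

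**The concern.** The groups form a 6 x 2 layout, and the scientific question lies in that layout: how does AF history relate to each parameter, and does the relation depend on the underlying disease? A two-sample test can compare AF with no AF inside one disease, or two diseases inside one AF stratum. It cannot combine the six within-disease AF contrasts into one estimate, and it cannot test whether they differ. Finding significance in one disease and not in another is no test of that difference.

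The second problem is confounding. Adults having congenital surgery and adults having coronary surgery may well differ in age. A t test passes any effect of age on conduction or voltage straight into the apparent disease difference. The study's product is a set of parameters for future studies to use in telling patients apart. A parameter that only reflects age would add nothing to knowing the patient's age.

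**Working it through.** **Inputs from the article.** 12 groups; at least 50 patients targeted per group; 8 listed parameters (conduction velocity, conduction block, fibrillation waves, epicardial breakthroughs, AF cycle length, dominant frequency, voltage, fractionation). **Assumed, because not stated:** two-sided 5% level, one value per patient and parameter, exactly 50 per group, and the size of any age effect.

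**The plan's own figures.** The worst-case half-width for a proportion is 1.96 x sqrt(0.25/n). At n = 50 this is 13.9% and at n = 300 it is 5.7%, which match the stated ±14% and ±6%. They are correct and unaffected by this point. They describe a single proportion, not a comparison of groups.

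**Confounding by age.** Suppose two disease groups differ in mean age by D SD, the parameter correlates r with age within groups, and disease has no effect. The unadjusted difference is then b = r x D SD. For example, D = 1 and r = 0.1 give 0.1 SD; D = 2 and r = 0.3 give 0.6 SD. With n per group the standard error is sqrt(2/n) SD, which is 0.20 at n = 50. Rejection rates from the noncentral t distribution:

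| Shift b (SD) | 50 v 50 | 100 v 100 |
|---|---|---|
| 0.1 | 8% | 11% |
| 0.2 | 17% | 29% |
| 0.4 | 51% | 80% |
| 0.6 | 84% | 99% |

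The nominal rate is 5%. More patients make the error more frequent, not less.

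**AF history and interaction.** Take a true AF-history effect of 0.3 SD, the same in all six diseases.
- One within-disease t test, 50 v 50: power 32%.
- One factorial model, 300 v 300 (balanced groups, no interaction): power 96%.
- Chance that all six separate tests agree: 0.32^6 + 0.68^6 = 0.001 + 0.099 = 0.10. So in about 90% of such studies some diseases would be significant and others not, which looks disease-specific when there is no interaction at all.

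**Number of tests (secondary).**
- One factor changed at a time: 15 disease pairs in each of 2 AF strata plus 6 AF contrasts = 36. Then 36 x 8 = 288 tests, and 288 x 0.05 = 14.4 expected false positives if there are no true differences.
- All pairs: 12 x 11 / 2 = 66. Then 66 x 8 = 528 tests and 26.4 expected false positives.
- Factorial model: disease, AF history and interaction = 3 tests per parameter. Then 3 x 8 = 24 tests and 1.2 expected false positives.

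**The case against.** The strongest reply is that the study calls itself exploratory and hypothesis-generating, accepts that it is underpowered for definite conclusions, and aims to discriminate between patients, which needs less than causal attribution. A journal article also condenses its protocol, so covariates and multiplicity rules may stand in a document not shown. Part of this stands. Strict error control is not obligatory here, and silence on multiplicity is not an error in itself. But the exploratory statement concedes power and precision only, and the Study Limitations section does not mention confounding between groups. Nor does the point rest on silence: the article names the test for patient groups and assigns regression to other comparisons.

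Several stronger readings are tempting but unsupported:
- **A reader might infer a pooled AF versus no-AF test that mixes disease with AF history.** No such test is planned. Splitting each disease by AF history sets up within-disease contrasts, and the only pooling mentioned, of 300 AF patients, concerns the precision of a proportion.
- **A reader might take the 66 pairs, multiplied by sites or quadrants, as the plan.** The article does not say that all pairs will be tested and states no significance level. The larger counts are ceilings.
- **A reader might hold the equal-variance assumption to be seriously violated.** A type I error near 13% needs, for example, 50 patients with SD 1.5 against 250 with SD 1.0, figures found nowhere in the article. At 50 v 50 with the same SDs, simulation gives about 5%.
- **A reader might conclude that differences between diseases will in fact be due to age.** Without age data this cannot be said; hence a range and not a single figure.

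**Conclusion.** The point holds in this limited form. The stated test does not fit the stated design: it leaves the disease by AF-history question untested and cannot separate disease from age. The size of the age problem is unknown. Over assumed shifts of 0.1 to 0.6 SD, the false-rejection rate at 50 v 50 runs from about 8%, a minor excess, to about 84%, which would make a disease comparison uninterpretable. The loss on AF history (32% against 96% power for 0.3 SD) assumes 50 per group, no interaction and no precision lost to covariate adjustment. Multiplicity is secondary: it affects how far a list of significant parameters can be trusted, not whether a difference is due to disease. The design is sound as it stands; the sentence on group comparisons should be changed.

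**What to change.** Replace the sentence on group comparisons with one patient-level linear model per parameter, containing disease, AF history and their interaction, adjusted for age and sex, with heteroscedasticity-robust standard errors. If several sites or quadrants per patient are kept, use a mixed model with a patient effect. Report the AF-history effect averaged over diseases and the interaction test, with estimates and 95% confidence intervals. Either control the false-discovery rate across parameters or state that findings are hypothesis-generating.

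Use left ventricular function only in a sensitivity analysis. It may be a consequence of the disease, so adjusting for it could remove part of the effect sought.

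The cost is slightly more analysis work and fewer nominally significant results, with no change to recruitment or mapping. Where the groups' ages overlap little, the adjusted comparison relies on the model, so the age distribution by group should be reported beside it. Adjustment for age and sex does not remove confounding by unmeasured factors, and conclusions about disease mechanisms should be worded accordingly.
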